### Missing data

We will analyze: 1) missing data longitudinally as a binary outcome at 6, 12, and 24 months, omitting the first time point; 2) separately, we will analyze which men drop out as a single binary outcome. Baseline sociodemographic variables (e.g., age, education) will be examined as predictors in each analysis; and 3) we will use intervention conditions as predictors of baseline sociodemographics. Any significant variables (analyses 1 and 2) and any sociodemographics that are predicted by condition (analysis 3) will be collected together and used as additional predictors in sensitivity analyses when assessing significance of the conditions.

Additional information is available as counts for several outcomes (e.g., number of days of drug use, number of partners) and continuous variables (CES-D, AUDIT) which we will analyze in secondary analyses. Among the subset of HIV-positive participants, we will analyze the HIV treatment continuum variables (i.e., linkage and retention in care, uptake and adherence to ARV). For binary outcomes measured at baseline and 6, 12, and 24 months, we expect to treat time categorically, and model main effects for condition, time, and time by condition interaction. Primary interest is the differences among conditions in the change from baseline to 12 months and to 24 months, and secondarily the change to 6 months. Assuming significant differences between conditions in changes from baseline, we will estimate pairwise differences (SL-V minus SL; SL minus CC; SL-V minus CC) in changes from baseline to months 6, 12, and 24.

Finally, we will summarize the frequency of practice elements delivered by coaches from process monitoring data in tables overall and by coach. We wish to see if supervisor ratings are predictive of practice element data that we collect; the model is longitudinal repeated measures but with coaches as the subject. Also, using GLMMs, we will analyze the process measures that are measured regularly (daily/weekly/monthly) during the soccer intervention to compare SL and SL-V conditions and to see how they relate to future employment. We expect that coaches who most frequently use goal setting and problem solving will have the young men with the greatest improvements. One year after the completion of data collection, a data set stripped of potential identifiers will be provided to the National Institutes of Health and available at UCLA.

Sample size calculations were carried out in two steps, similar to our previous studies in this area [66], to achieve 80% power with a 0.05 alpha level. First, calculations were carried out to compare two conditions (e.g., SL-V versus SL) on a dichotomous outcome, since dichotomous outcomes generally require larger sample sizes than continuous outcomes. Using employment as an example, we assume an employment rate of 30% at 12 or 24 months in one of the conditions. The sample size will achieve sufficient power if the other condition has 17% (or less) or 41% (or more) employment. We anticipate actual employment differences between groups bigger than 13% (= 30% – 17%) or 11% (= 41% – 30%). We assume 20% loss to follow-up (the pilot had 5% loss at 6 months). This sample size calculation estimates the total sample size for two groups. The additional sample needed for the third group is simply the total sample size divided by two. As a second step, the total sample size is inflated to account for the double nesting of men within teams and teams within neighborhoods. We apply the design effect adjustment (1 + (*n* – 1) × rho) twice, where *n* is the cluster sample size (17 participants per team at the most, and 50 participants per neighborhood) and we take the intraclass correlation (rho) to be 0.01, consistent with previous studies in these neighborhoods [66]. The design effect for our study is the product of these two effects, 1.49 × 1.16 = 1.7284. The CC condition has less design effect than the SL and SL-V conditions, but we have conservatively adjusted the calculations for both design effects across all three conditions; alpha = 0.05, power = 0.8. After carrying out the second step, we arrive at our target sample size of 1200 participants, with 400 per condition. As we will have longitudinal data on employment, our analysis will actually offer smaller standard errors of estimation, and thus we expect to have even greater power than this. In our pilot, 40% of young men had used hard drugs [11]. Comparing two conditions, we have power to detect a decrease to 26% in SL or SL-V from CC. Since for drug use and other analyses we get to adjust for baseline hard drug usage, the power improves substantially.

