### Outcome measures

The primary outcome is the NSO out of 15 outcomes, as explained by Harwood et al. [49]. The 15 specific outcomes are explained below, along with how we intend to analyze each outcome. We analyze each outcome separately. We count the number of outcomes out of 15 where the treatment effect is significant at *p* = 0.05 (two-sided) and that count is the NSO. The single NSO outcome allows us to identify the outcomes affected by the intervention while adjusting for multiple comparisons and the correlations among the outcomes. For fifteen outcomes, the NSO needed for a significant result is either 2 or 3 outcomes, depending on the correlation among the outcomes. As a practical matter, the cutoff is 2 only if the correlation among outcomes is near 0 or near 1. For correlations among outcomes between 0.1 and 0.9 (see Table 2 of Harwood et al. [49]), three significant outcomes give significance at the 0.05 level and, based on similar work with similar variables in these same neighborhoods of Cape Town, we plan to require a minimum of three significant outcomes to declare that the treatment is effective.

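### The sample size does not give 80% power for employment of 41% versus 30%: the plan's own inputs give about 60%, and the detectable rate is about 44%

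*Protocol article*

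**What the plan says.** The sample-size paragraph sits at the end of the Missing data section. It aims "to achieve 80% power with a 0.05 alpha level" in a comparison of two conditions on a binary outcome. Employment is the worked example: "we assume an employment rate of 30% at 12 or 24 months in one of the conditions". It continues: "The sample size will achieve sufficient power if the other condition has 17% (or less) or 41% (or more) employment". The next sentence repeats the two bounds as differences of 13 points (30% to 17%) and 11 points (30% to 41%), and says the investigators expect larger ones.

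The paragraph assumes 20% loss to follow-up. It then inflates for men nested in teams and teams nested in neighborhoods, with an intraclass correlation of 0.01 and a combined design effect of 1.49 × 1.16 = 1.7284 applied to all three conditions. It ends: "After carrying out the second step, we arrive at our target sample size of 1200 participants, with 400 per condition".

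Two further points bear on the check. The same paragraph gives a second example, hard drug use falling from 40% to 26%. It also describes the benefit of longitudinal data as coming on top of the stated power. The Outcome measures section says each outcome is tested two-sided at 0.05.

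**The concern.** The two bounds look wrong before any calculation. The variance of a proportion grows as the rate moves from 30% towards 50% and shrinks as it moves towards zero. At a fixed sample size the smallest detectable rise from 30% must therefore be larger than the smallest detectable fall. The plan has it the other way round: 11 points up, 13 points down.

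Employment is one of the 15 primary outcomes, and a rise is what the vocational training is meant to produce. If the 11-point figure is wrong, the article promises 80% power where the design does not have it. Readers could then take a null employment result as stronger evidence against an 11-point gain than it would be.

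**Working it through.** **Inputs.** From the sample-size paragraph: 400 per condition, 20% loss, design effect 1.7284, alpha 0.05, power 0.80, reference rate 30%. From Outcome measures: two-sided test. Hence z(α/2) = 1.96 and z(β) = 0.8416.

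**Effective size per condition.** m = 400 × 0.8 / 1.7284 = 185.1.

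**Formulas** (two proportions, pooled variance under the null, p̄ the mean of p₁ and p₂):

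- n = [1.96 √(2p̄(1−p̄)) + 0.8416 √(p₁(1−p₁) + p₂(1−p₂))]² / (p₁−p₂)²
- power = Φ{ [|p₁−p₂| √m − 1.96 √(2p̄(1−p̄))] / √(p₁(1−p₁) + p₂(1−p₂)) }

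**Worked case, 30% versus 41%.** Here p̄ = 0.355, so √(2p̄(1−p̄)) = 0.6767. The other root is √(0.21 + 0.2419) = 0.6722.

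- n = (1.96 × 0.6767 + 0.8416 × 0.6722)² / 0.11² = 295.9 per condition before inflation
- × 1.7284 = 511; / 0.8 = 639 per condition; × 3 = about 1,918 in total (about 640 and 1,919 if n is first rounded up to 296)
- power at m = 185.1: (0.11 × 13.61 − 1.326) / 0.6722 = 0.253, and Φ(0.253) = 0.60

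**All the stated figures, checked the same way:**

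| Comparison | n before inflation | n per condition after design effect and loss | Power with 400 per condition |
|---|---|---|---|
| 30% v 17% (stated) | 165.8 | 358 | 0.84 |
| 40% v 26% (stated) | 175.9 | 380 | 0.82 |
| 30% v 41% (stated) | 295.9 | 639 | 0.60 |
| 30% v 44% (not stated) | 185.5 | 401 | 0.80 |

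At m = 185.1 the rates that give exactly 80% power are 17.6% and 44.0% against 30%, and 26.3% against 40%. So the plan's 17% and 26% are reproduced. Only 41% is not.

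**Choice of formula.** For 30% versus 41%, unpooled variance gives power 0.605, the arcsine formula 0.602, and a continuity correction about 0.56. With the continuity correction the other two figures still hold (391 and 410 per condition, power 0.81 and 0.79), and 41% needs 678.

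**Other readings of the inputs** (30% v 41%, 400 per condition, pooled formula):

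| Variation | Power |
|---|---|
| No loss, full design effect | 0.70 |
| 5% loss (the pilot's 6-month figure), full design effect | 0.67 |
| 20% loss, neighborhood effect only (1.49) | 0.66 |
| 20% loss, team effect only (1.16) | 0.77 |
| 20% loss, additive design effect (1 + 0.49 + 0.16 = 1.65) | 0.62 |
| 20% loss, cluster sizes reduced by 20% | 0.64 |
| 20% loss, reduced cluster sizes and additive effect | 0.66 |
| 20% loss, no design effect | 0.83 |
| One-sided, 20% loss, full design effect | 0.72 |
| One-sided, no loss, full design effect | 0.80 |

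Two rows reach 80%. One drops the design effect, which the paragraph says was applied. The other drops both the stated loss and the stated two-sided test, and on that basis 30% versus 17% would need only 226 per condition, so it cannot have produced the plan's 17%.

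**The case against.** The strongest reply is that little hangs on this figure. Employment is offered as an example and is one of 15 outcomes. The trial declares success when at least three of them are significant, and 41% enters neither that rule nor the analysis. The target of 400 per condition is supported by the other two examples. All of this is true, and it limits the consequence: neither the design nor the analysis needs to change. It does not make the printed power correct.

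A second reply is that the calculation simplifies the planned analysis, a two-degree-of-freedom test of change from baseline in a hierarchical model, and that the plan itself calls its design effect conservative for the control condition. With 1.49 for control and 1.7284 for the soccer condition, power at 41% rises only to about 0.63. The gain from repeated measures cannot fill the gap either, because the paragraph presents it as additional to the 80%. Reaching 80% at 41% that way would need a baseline-to-outcome correlation of about 0.61 (sample size multiplied by 1/(1−r²)). That value is an assumption; the document gives none.

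A third reply is that the source of 41% cannot be known. That stands. It could be a slip for 44%, or a calculation that left out some or all of the clustering: with 20% loss, the 80% limit is 40.6% with no design effect and 41.4% with the team effect alone. The document does not settle which. It is also fair that nothing in the plan says a null employment result will be read as excluding an 11-point gain; that is a risk, not a planned inference.

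**Conclusion.** The concern holds. On the plan's own inputs, power for 30% versus 41% employment is about 60%, not 80%, so a true 11-point gain would be missed about 40% of the time rather than 20%. The upward rate detectable with 80% power is about 44%, a gain of 14 points. The error is confined to the 41% bound and the 11-point difference derived from it; 17%, 26% and the target of 1,200 are consistent with one another.

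This rests on a two-sided pairwise comparison of proportions under large-sample theory, with the stated loss and design effect. Allowing for only eight neighborhoods per condition would lower power further.

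**What to change.** In the sample-size paragraph, change 41% to 44% and the 11-point difference (41% minus 30%) to 14 points (44% minus 30%). Alternatively, keep 41% and state that power there is about 60%. The sponsor should rerun the original calculation to confirm which correction applies, and check that the investigators still expect an employment gain larger than the corrected limit.

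The cost is two edited sentences and one less favorable figure. No participants are added, and the target of 1,200, the randomization and the analysis are unchanged.

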One explanation for men’s underutilization of healthcare is the incompatibility of existing intervention models with young men’s identities, roles, and preferred styles of acting [11, 24, 25]. Existing evidence-based interventions (EBI) for HIV are based on counseling models of “tend and befriend”, which are common female strategies for coping with stress [26]. In contrast, men more often utilize a “fight or flight” strategy for coping with stress [26]. Traditionally, men’s engagement in EBI for HIV has been lower than that of women [27].

Young South African men need new pathways for prosocial roles and behaviors. Concurrently, interventions need to be attractive and consistent with men’s styles. We have designed a behavioral intervention around soccer to “pull” or engage men in the intervention, rather than having to “push” public health strategies into their lives. For men, sports activities are highly attractive activities and promote a social and personal identity [28]. South Africans associate soccer with a strong sense of national identity [29] and sports elicit strong feelings of masculine identity [30]. Soccer potentially creates a replacement for the strong masculine roles in tribal society that were destroyed with rapid migration to peri-urban settlements in the Western Cape of South Africa. In the context of having fun or planning for the future, young men acquire healthy habits of daily living and reinforce positive community norms. In our pilot study, soccer was a highly desirable activity; 95% of men enrolled in the pilot and 80% were successfully engaged on a sustained basis, participating in roughly three practices and a game weekly over 6 months [11]. Even if they were not good players, the young men valued being part of the team. In qualitative interviews, families felt uniformly positive about soccer. It occupied young men, gave them respect in the community, and games were an opportunity for the community to attend and value the young men.

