#### Condition 2: soccer league (SL)

All young men in eight neighborhoods (*n* = 400) receive soccer training for 1 year. After all of the baseline assessments are completed in a specific neighborhood, soccer coaches visit each participant individually to describe the intervention in detail, invite them to the soccer league, and answer any questions. The league includes at least two and usually three teams per neighborhood (14 men minimum per team needed, anticipating some absenteeism), resulting in approximately up to 24 teams in this condition. Each week, there are 2 days of practice and 1 day for a game with another team. Teams are led by coaches who are recruited from the broader township (versus target neighborhoods) to safeguard players’ confidentiality (coming from the same neighborhood is likely to inhibit men’s disclosures about problem issues, fearing the coach may tell others). Coaches cannot be regulars at the local shebeens or known drug addicts, and must have held a job at some time previously, have experience playing soccer, and demonstrate good social skills. In this way, coaches are positive peer deviants (i.e., role models) for participants [53, 54]. About 30% of persons applying to be coaches are hired, based on initial interviews and observations completed during the coach training.

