While working in townships and outside of clinical settings may help engage high-risk men in the intervention, it also creates challenges and limitations. Because the intervention is largely carried out on the soccer field rather than in a clinic or university, many resources (i.e., nurses and physicians, treatment, counseling, and laboratory testing facilities) are not available onsite. Furthermore, as Dishion et al. and Kaminer have demonstrated, risky young men can serve to disinhibit the harmful and delinquent behaviors of peers in group interventions [70, 71], particularly if most of the young men already engage in high-risk behaviors such as substance use. These challenges are addressed in multiple ways. Testing for HIV and substance use is easily conducted outside the laboratory by coaches and assessors using RDT with mobile integration. To combat risky group behavior, coaches serve as role models who can influence young men by example and share their normative beliefs around HIV, alcohol and drug use, and the daily routines that protect against risky behaviors. Diffusion of innovation theory and our experience with popular opinion leader interventions both posit that 15% of the group behaving as positive peer leaders is enough to diffuse positive norms and build toward a tipping point [72, 73]. Coach training includes specific strategies to combat the development of norms increasing risky behaviors among the men in addition to behavioral management strategies, and familiarity with important resources for referral as needed. A month of full-time training for coaches is considerable and, some argue, non-replicable. Our proposed coach training is a similar length to that of the broadly-scaled CHW training through the Philani Maternal, Child Health and Nutrition Project [66]. However, the coaches are able to contact 28 young men daily (with two teams of at least 14 men each), not the typical four home visits per day by CHWs.

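### The design effect of 1.7284 is not that of the nested design and is mildly conservative, but the detectable employment rate of 41% fails under it and under every corrected value

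*Protocol article*

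**What the plan says.** The sample size text stands at the end of the Missing data section. It aims "to achieve 80% power with a 0.05 alpha level" for a comparison of two conditions on a binary outcome. For employment, "we assume an employment rate of 30% at 12 or 24 months in one of the conditions", and the other condition is said to be distinguishable at 17% or lower, or at 41% or higher. For hard drug use it claims power for a fall from 40% to 26% in either soccer condition against control. Loss to follow-up is taken as 20%.

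The one-level factor 1 + (n − 1)ρ is applied twice with ρ = 0.01 and cluster sizes of "17 participants per team at the most, and 50 participants per neighborhood". Then "The design effect for our study is the product of these two effects": 1.49 × 1.16 = 1.7284. The text acknowledges that control has less clustering and describes using both factors in all three conditions as conservative. The target is 400 per condition, 1200 in all.

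The section on Condition 2 plans "at least two and usually three teams per neighborhood (14 men minimum per team needed, anticipating some absenteeism". The Data analysis section specifies random effects for neighborhood, for team within neighborhood, and for men.

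**The concern.** The planned model has two nested sources of clustering whose variances add. Multiplying two one-level factors, each with its full cluster size, counts part of the clustering twice. The factor also uses enrolled sizes although a fifth of the men are assumed lost, and it takes 17 as the largest team although two teams for 50 men means 25 each. The target and the detectable differences are presented as resting on this factor. If it is wrong, the stated differences may not be those that 400 men per condition can detect, in either direction.

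**Working it through.** **Inputs.** From the sample size text: power 0.80, α = 0.05, rates 30/17, 30/41 and 40/26%, 20% loss (320 of 400 analysed per condition), ρ = 0.01, sizes 17 and 50. From the Condition 2 section: two or three teams per neighborhood. Assumptions: a two-sided test (the Outcome measures section tests each outcome at "0.05 (two-sided) and that count is the NSO"), all men placed on teams, and a team correlation of 0.01 on top of the neighborhood's 0.01.

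**Step 1: the plan's own figures.** (1 + 49 × 0.01)(1 + 16 × 0.01) = 1.49 × 1.16 = 1.7284, as stated. The number per arm for two proportions is n = [1.96√(2p̄q̄) + 0.842√(p₁q₁ + p₂q₂)]² / (p₁ − p₂)², where p̄ is the mean of the two rates and q = 1 − p. It is then multiplied by 1.7284 and divided by 0.8. Values in brackets use the continuity correction.

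- 30% v 17%: 166 (181) per arm, giving 359 (391). This agrees with 400.
- 40% v 26%: 176 (190) per arm, giving 380 (410). This agrees with 400.
- 30% v 41%: 296 (314) per arm, giving 640 (678), or about 1920 to 2034 for three conditions. This does not agree. Without the design effect, 314 / 0.8 = 393, which does.

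**Step 2: the design effect of the nested model.** DE = 1 + (n_N − 1)ρ_N + (n_T − 1)ρ_T, where N is neighborhood and T is team.

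- Enrolled, 50 and 17: 1 + 0.49 + 0.16 = 1.65. The product adds a cross-term, 0.49 × 0.16 = 0.0784, that the model does not contain.
- A product is valid if its second factor uses the number of teams and the correlation between team means. With three teams: (1 + 15.67 × 0.02)(1 + 2 × 0.127) = 1.65. A simulation of 50-man neighborhoods also gave 1.65.
- If 0.01 is the whole correlation between teammates, the enrolled value is 1.49.
- Retained, 40 men in three teams of 13.3: 1 + 0.39 + 0.123 = 1.51.
- Retained, 40 men in two teams of 20: 1 + 0.39 + 0.19 = 1.58.
- Control, retained, no teams: 1 + 0.39 = 1.39.
- Enrolled, two teams of 25: sum 1 + 0.49 + 0.24 = 1.73; product 1.49 × 1.24 = 1.8476.

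**Step 3: power and detectable rates.** Effective men per arm = 320 / DE, same DE in both arms, no continuity correction.

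| DE | Effective n | Power 30 v 17 | Power 40 v 26 | Power 30 v 41 | Detectable: 30 down / 40 down / 30 up |
|---|---|---|---|---|---|
| 1.7284 | 185 | 84% | 82% | 60% | 17.6 / 26.3 / 44.0% |
| 1.65 | 194 | 86% | 84% | 62% | 17.9 / 26.6 / 43.7% |
| 1.58 | 203 | 87% | 85% | 64% | 18.1 / 26.9 / 43.4% |
| 1.51 | 212 | 89% | 87% | 66% | 18.4 / 27.2 / 43.1% |
| 1.00 | 320 | 97% | 97% | 83% | 20.4 / 29.5 / 40.6% |

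Against control at 1.39, with the soccer arm at 1.51 to 1.58, power for 40% v 26% is 88–87% and for 30% v 41% 68–67%. For 80% power at 41% the design effect could be at most 320 / 296 = 1.08, below either one-level factor alone.

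**Step 4: optional sensitivity.** Under an assumed ρ_T of 0.05, a value the document does not give, DE is 1 + 0.39 + 12.33 × 0.05 = 2.01 (three teams) or 1 + 0.39 + 19 × 0.05 = 2.34 (two teams). Power for 30% v 17% between the two soccer conditions is then about 79% to 72%. For 40% v 26% against control (DE 1.39 there) it is about 82% to 79%.

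**The case against.** The best defence is that, on the plan's correlation, the factor errs on the safe side. The product exceeds the sum, enrolled sizes exceed retained ones, and the extra control adjustment is disclosed. Even the additive form with 25-man teams gives 1.73, the stated value by coincidence. The 17% and 26% figures move by about one point or less. Only the product with 25-man enrolled teams (1.8476) takes 40% v 26% just under 80%, to 79%. All of this stands, and it makes the product-versus-sum point minor by itself. It does not help 41%, which fails at 1.7284 too. The plan also expects gains from longitudinal data and baseline adjustment, but it gives them no size and presents them as additional to the stated figures.

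Three stronger readings are tempting, and the document does not support them.

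- A reader might infer that all the stated differences are too pessimistic. That is true of 17% and 26% and false of 41%.
- A reader might infer that the team correlation has no basis, because the Discussion links the cited reference to "CHW training through the Philani Maternal, Child Health and Nutrition Project [66". That reference is not at hand, so what it supports cannot be judged. Peer influence appears in the article as a hazard to monitor and counter, not as a predicted team correlation, and the Data analysis section expects one or other variance to be small for many outcomes.
- A reader might infer that three teams cannot be filled, since in the pilot "80% were successfully engaged on a sustained basis" and 80% of 50 is 40, fewer than 3 × 14 = 42. Men can be on a team without sustained attendance, so this is not shown. Three teams is the usual plan, and 50 / 3 is where 17 comes from. What remains is a mismatch between a stated maximum of 17 and a stated minimum of two teams.

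**Conclusion.** The point holds in a limited form. The factor 1.7284 is not the variance inflation of the planned nested model. With ρ = 0.01 at each level that is 1.65 at enrolled sizes, and 1.51 to 1.58 in the soccer conditions and 1.39 in control at retained sizes. The effect on the target is harmless: 30% v 17% has about 87–89% power and 40% v 26% about 85–88%.

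The material error is 41%. Power there is 60% on the plan's own factor and 64–66% on the corrected ones (67–68% against control without a team term). The rate detectable with 80% power is about 43–44%, so the upward difference is 13 to 14 points, not 11. The figure fits a calculation in which the design effect was left out, though the document does not say that this happened.

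These results assume a two-sided normal test of two proportions, equal cluster sizes and all men on teams. The figures at ρ_T = 0.05 show sensitivity only. Nothing here shows that 1200 men is the wrong target.

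**What to change.** Reword the sample size paragraph:

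- Replace the product by 1 + (n_N − 1)ρ_N + (n_T − 1)ρ_T with the cluster sizes expected at analysis. State whether 0.01 at team level is additional to the neighborhood correlation.
- Reconcile the team maximum of 17 with the Condition 2 section, for example by giving the factor for both three and two teams.
- Restate all three detectable rates and their power at 400 per condition: about 18% from 30%, about 27% from 40%, and about 43–44% in place of 41%. Alternatively keep 41% and state its power as about 60–66%. Correct the 11-point difference to match.
- Optionally add one line on a larger team correlation, marked as an assumption, with no team term in control.

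The cost is a rewritten paragraph. Enrolment, design and analysis stay as they are.
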